### Recruitment and allocation

The researcher in each region will present the study and provide written information about the study to eligible parents before they are discharged from the hospital (Fig. 1. Timeline SWEpap study). When the parent-infant dyads return to the postnatal care unit for the metabolic screening test, they will be asked to participate and to sign the consent form (both the mother and her partner). The parents who have accepted to participate are then randomly assigned to one of the three interventions groups using the sealed opaque envelope system with randomly generated treatment allocations administered by an impartial researcher. Once the parents have consented to enter the trial, the researcher opens the envelope and the allocated treatment regimen is offered to the parents. The researchers will then guide the parents in each group how to position themselves and the infant and if applicable how to use live parental lullaby singing. If the parent does not adhere to the protocol in the allocated treatment group, the infant will be excluded from the study.

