### Study design

This is a multi-center, randomized controlled trial (RCT) with three parallel groups with the allocation ratio 1:1:1.

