### Sample size

No previous RCT has examined the effects of parent-driven pain management in newborn infants by combining SSC, breastfeeding and live parental lullaby singing. Based on previous studies using PIPP-R or its predecessor PIPP in pain alleviation projects, a difference of two PIPP-R points between standard care (group 1) and the full parent driven pain management (group 3) is considered clinically important. Based on those studies we also assume a standard deviation around 2 points. A power calculation sets the number of infants to include in the study to 63 in each group, with a power of 0.8 and a significance level set to 0.05 (www.clincalc.com). To compensate for possible dropouts, incomplete data, such as equipment malfunction or blood sample collection failure, 75 infants per group will be enrolled, making a total of 225 infants.

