## Methods: data collection, data analyses and management, data monitoring

### Data collection

Demographic data of the parent-infant dyad is registered before the procedure starts, including registration of potential music and singing activities during pregnancy for the parents in group 3. In all groups: before, during and after the procedure the infant will have a saturation probe attached to one foot making it possible to measure heart rate and oxygen saturation and electrodes measuring galvanic skin response on the other foot. The infant’s face and pulse oximetry values will be videotaped for later pain assessment with PIPP-R. An experienced midwife/nurse will perform the venipuncture. Venipuncture is routinely used in all hospitals in Swedish neonatal and postnatal care since it is considered less painful for the infant than heel lance [56]. A tourniquet using a soft cotton band is applied, the skin is disinfected, and a 21–23 Gauge needle is used for the blood sampling. The infant will be monitored until the treatment is concluded. In case of failed attempts, only the first venipuncture will be used in the study. In the breastfeeding condition, the midwife/nurse will make sure that the infant is latched and sucking well before the blood test is performed to safeguard the analgesic effect of breastfeeding. The infants’ behavioral responses to pain together with oxygen saturation and heart rate values are videotaped with two digital video cameras and will be assessed subsequently from the video films.

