### Data analyses, management and monitoring

Methods for statistical analyses are chosen depending on scales of measurement and normal distribution. The data will be analyzed with descriptive and comparative statistics. Continuous variables that are normally distribute will be presented with mean and standard deviation and compared with t-test for two groups and ANOVA for multiple groups. For data that doesn’t fulfil those criteria we will use median with interquartile range and Mann-Whitney U-test or Kruskall-Wallis one way analysis of variance, respectively. Intention-to-treat will be used, including all randomized parent-infant dyads in the analysis. The division of group 2 into 2a and 2b, which is a nomenclature to distinguish breastfeeding from no breastfeeding, will be taken into account in the comparative analyses and differences between the two subgroups will be scrutinized. Cohens kappa will be used to calculate interrater reliability between PIPP-R scorers.

The data collected in the study is safely stored on a secure server at Örebro University. The project folder on the server is only available to the researchers in the project and is automatically backed-up. The principal investigator is responsible for the data monitoring, ensuring that the researchers in the study are carrying out the research according to the research protocol, ensuring intervention fidelity in the live parental lullaby singing via recurring spot checks with microanalysis of the live singing, ensuring the research is keeping to time and budget and that the research is being conducted ethically. The research group will meet regularly to ensure consistency. During the original development of the project proposal of the SWEpap-study, the research group consulted with parents with previous extensive experience of NICU care. These parents will continue to give feedback on demand.

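### Excluding non-adherent dyads after randomisation contradicts the declared intention-to-treat analysis of all randomised dyads, and may bias the group 1 versus group 3 comparison

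*Protocol article*

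**What the plan says.** The design is a "randomized controlled trial (RCT) with three parallel groups with the allocation ratio 1:1:1" (Study design). Recruitment and allocation gives the order of events: "Once the parents have consented to enter the trial, the researcher opens the envelope and the allocated treatment regimen is offered to the parents". The same paragraph ends with the exclusion rule: "If the parent does not adhere to the protocol in the allocated treatment group, the infant will be excluded from the study".

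Data analyses, management and monitoring names the analysis population: "Intention-to-treat will be used, including all randomized parent-infant dyads in the analysis".

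Table 1 sets out what each arm asks of the parent. In group 1 the infant lies on the examination table, and a nurse can do the tucking and offer a finger to suck. In group 3 the parent holds the infant skin to skin and hums from 10 minutes before the venipuncture until some time after it, with breastfeeding where applicable. The Discussion expects that some parents will be inhibited about singing. The article gives no definition of non-adherence and no expected rate in any arm.

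**The concern.** An intention-to-treat analysis keeps each randomised dyad in its allocated group whatever happens afterwards. A dyad excluded from the study for non-adherence cannot be in that analysis. If the exclusion rule is applied, the primary comparison is per-protocol under an intention-to-treat label.

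The label matters less than the comparability of the arms. Random allocation makes the arms comparable at the moment the envelope is opened. Removing dyads for what happens later keeps that comparability only if the removals are unrelated to the pain score or balanced between arms. Neither can be assumed here. The arms ask different things of the parent, and the fidelity checks described under data monitoring concern the singing, so deviations are most likely to be noticed in group 3. The PIPP-R score comes from the first 30 s of the procedure, while skin-to-skin contact and humming are meant to continue through it. Non-adherence could therefore be a response to the infant's distress. Blinded scoring of muted video does not help if the recording has already been removed or was never made.

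**Working it through.** **1. The two rules side by side.** Consent, then the envelope, then the regimen is offered, then adherence or not. Non-adherence to an allocated group cannot occur before allocation. The first rule removes such infants from the study as a whole and not only from one analysis set. The second includes all randomised dyads. They agree only if nobody deviates. No other section limits the exclusion to a per-protocol set or says that outcomes are still collected on non-adherent dyads.

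**2. The plan's figures.** This point contests none of them. The enrolment target implies an allowance for losses of 1 − 63/75 = 16%, and 63/0.84 = 75 as stated. The reasons given for it are dropout and incomplete data; non-adherence is not named. (How 63 follows from the stated difference and SD is a separate question and does not affect this point.)

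**3. Possible size, on assumed values.**

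From the article: 75 per arm; "we also assume a standard deviation around 2 points"; target: "a difference of two PIPP-R points between standard care (group 1) and the full parent driven pain management (group 3) is considered clinically important".

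Assumed: no true effect; exclusions in group 3 only; share excluded p; correlation r between the pain score and a latent tendency not to adhere, those with the highest tendency being excluded.

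- Gap between excluded and retained infants = r × SD × φ(z) / [p(1 − p)], where z cuts off the upper share p of a standard normal and φ is its density.
- Bias in the group 3 mean = p × gap, towards lower pain.
- SE of the difference = 2 × √[1/75 + 1/(75(1 − p))].
- Two-sided type I error ≈ Φ(bias/SE − 1.96) + Φ(−bias/SE − 1.96).

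For p = 0.10, φ(z) = 0.1755 and SE = 2√(1/75 + 1/67.5) = 0.335. For p = 0.20, φ(z) = 0.280 and SE = 2√(1/75 + 1/60) = 0.346.

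| p | r | Gap (points) | Bias (points) | Type I error, formula | Type I error, simulated |
|---|---|---|---|---|---|
| 0.10 | 0 | 0 | 0 | 5.0% | about 5% |
| 0.10 | 0.3 | 0.3×2×0.1755/0.09 = 1.17 | 0.12 | 6.4% | 6.1–6.5% |
| 0.10 | 0.5 | 0.5×2×0.1755/0.09 = 1.95 | 0.20 | 8.9% | 8.9–9.2% |
| 0.20 | 0 | 0 | 0 | 5.0% | about 5% |
| 0.20 | 0.3 | 0.3×2×0.280/0.16 = 1.05 | 0.21 | 9.3% | 9.2–9.4% |
| 0.20 | 0.5 | 0.5×2×0.280/0.16 = 1.75 | 0.35 | 17% | 17–18% |

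The simulated ranges come from repeated runs of 20,000 trials each. A bias of 0.35 points is 0.35/2 = 17.5% of the target difference.

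**4. If group 1 also loses dyads.** With 10% excluded in each arm and the same excess pain in those excluded, the biases cancel and the type I error is 5.0%. With 5% excluded in group 1, 20% in group 3 and a 2-point excess in both, the bias is (0.20 − 0.05) × 2 = 0.30 points and the type I error about 14%. If more distressed infants were removed from group 1 than from group 3, the bias would run against the parent-driven arm.

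**The case against.** The strongest reply is that the contradiction is real but the direction of bias is not shown. That stands. The article has no adherence rates and nothing on how excluded infants would have scored. The one difficulty it foresees, shyness about singing, is a trait of the parent with no stated link to infant pain, and without such a link there is no bias. Group 1 parents may deviate too: at one hospital standard care has no glucose and consists of skin-to-skin contact and breastfeeding, and the Discussion regards preventing breastfeeding as ethically unacceptable. A group 1 parent who picks up or feeds a distressed infant would also fall under the rule.

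Three stronger readings are tempting, and the article does not support them.

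- A reader might infer that unsettled infants who fail to latch are removed from group 3. The rule concerns the parent's adherence, breastfeeding in group 3 applies only where applicable, and latching is a condition for starting the blood test, not a ground for exclusion.
- A reader might assume that excluded infants score 2 to 3 points higher, giving a bias of 0.4 to 0.6 points at 20% excluded. With SD 2 that needs r = 2 × 0.16/(2 × 0.280) = 0.57 up to 3 × 0.16/(2 × 0.280) = 0.86, above the values used here. A 20% loss to non-adherence in one arm also exceeds the plan's whole 16% allowance.
- A reader might see a second conflict between "To compensate for possible dropouts, incomplete data, such as equipment malfunction or blood sample collection failure, 75 infants per group will be enrolled" and "In case of failed attempts, only the first venipuncture will be used in the study". The first only gives a reason for over-enrolling, and an attempt abandoned early may not yield the 30 s that PIPP-R needs.

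It may also be said that a statistical analysis plan could settle the matter. It could define the sets, but it cannot recover outcomes that were never recorded because the infant had been excluded.

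**Conclusion.** Wrong as written. The exclusion rule and the intention-to-treat rule are both current text and cannot both be followed. If the exclusion is applied, the primary comparison is not intention-to-treat and no longer rests on randomisation alone. This conclusion needs no assumption and is firm.

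That exclusions will be unequal between arms is likely, given the different tasks in Table 1. That they favour the parent-driven arms is possible but not established. The illustration runs from no bias (no correlation, or balanced exclusions) to about 0.35 points with a type I error of about 18% (20% excluded in group 3 only, correlation 0.5). The shares, the correlations and the restriction to group 3 are all assumptions; only the 75 per arm and the SD of about 2 come from the article.

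**What to change.** Replace the exclusion sentence under Recruitment and allocation with a rule along these lines:

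- Every randomised dyad stays in the primary analysis in its allocated group.
- The first venipuncture is still filmed and scored whatever the adherence, unless the parents withdraw consent, which they may do at any time.
- Adherence is defined for each arm, recorded, and reported by arm.
- Exclusion for non-adherence is used only in a secondary analysis labelled per-protocol.

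The intention-to-treat sentence can then stand. The cost is a few sentences and an instruction to the sites to keep recording; no sample-size figure changes. It should be in force before data collection, or as early as possible, because unrecorded procedures cannot be scored later. The small downside is that the intention-to-treat effect may be somewhat smaller than the per-protocol effect.

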Group 3	Parent-driven pain management with a combination of skin-to-skin contact, breastfeeding and live parental lullaby singing	The intervention in the combination group will follow the above described skin-to-skin and breastfeeding treatment descriptions. The parents are also instructed to hum a lullaby with their infant. The parent starts humming the lullaby when the infant is placed on the parent’s bare chest 10 min before the venipuncture and continues during and a while after the procedure. The humming should be performed in a simple, repetitive, soft and sedative mode in a low pitch, in consonant harmony, with a slow, steady and predictable pulse of 3/4 or 6/8 rhythm, maintaining a constant sound level between recommended ≤55–65 dB on the A-scale [49].

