### Interventions

The treatment groups in the RCT are described in Table 1. Group 2, comprising SSC, is divided into two subgroups, one with only SSC and one where the mother also chooses to breastfeed her infant during the test. The reason for these subgroups is that standard of care in one of the hospitals does not include glucose but comprises only SSC and breastfeeding when applicable. To ensure intervention fidelity in the live parental lullaby singing, a short video, showing a parent who sings according to the treatment description of the lullaby singing, will be played for the parents who are randomly assigned to group 3. These parents will also be verbally guided in how to sing before the intervention starts. The verbal instructions are simplified and delivered in dialogue with the parent who can ask questions.

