To reduce the risk for selection bias in this study, broad inclusion criteria will be used including also parent-infant dyads from other cultures who understands English or Swedish, which strengthens the results and generalizability. A strength in this study is that data collection will take place in four hospitals in diverse health care regions in Sweden which will hopefully increase the scientific quality by recruiting a large sample size within a feasible time period, increasing the generalizability to other settings and reduce the risk of recruitment bias. The allocation with group 2a and b, referring to two different groups receiving skin-to-skin contact, might be considered as problematic. However, performing clinical research sometimes makes it difficult to use standardized procedures. It is not ethically feasible to defer from already existing guidelines and, in this study, preventing mothers from breastfeeding if applicable. It is important to focus on relevant clinical situations where the results can be useful for the patients, families and various health care settings and not only conducting research in laboratory surroundings. An aspect that must be taken into consideration is how to empower parents to use their voice and sing in conjunction with painful procedures. Parents might feel shy and inhibited about singing, especially in unfamiliar situations among unfamiliar people. On the other hand, research shows that most parents (60%) already sing spontaneously to their newborn during hospitalization [73]. By starting the lullaby singing together with SSC 10 min before the venipuncture and giving the parents clear instructions how the singing should be performed, we might modulate possible concerns. The use of technical equipment during the venipuncture will add a few minutes to the procedure, however the research group has previous extensive experience of similar research projects that will ensure the implementation of the study protocol.

The results generated in the SWEpap study will hopefully contribute to the interdisciplinary endeavor world-wide of involving and integrating parents in neonatal pain management and presumably also inform pain management practice in the neonatal intensive care context, where the critically ill and vulnerable hospitalized infants suffer the most from repeated, cumulative and inadequately treated procedural pain in addition to separation from the parents.

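### Infants of non-adherent parents are excluded after randomization, although the analysis is promised as intention-to-treat in all randomized dyads

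*Protocol article*

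**What the plan says.** The section Recruitment and allocation gives the order of events. Consent comes first, and then "The parents who have accepted to participate are then randomly assigned to one of the three interventions groups". The next step is: "Once the parents have consented to enter the trial, the researcher opens the envelope and the allocated treatment regimen is offered to the parents". Parents are then guided in how to carry out the regimen. The section closes with the rule at issue: "If the parent does not adhere to the protocol in the allocated treatment group, the infant will be excluded from the study".

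The section Data analyses, management and monitoring defines the analysis population: "Intention-to-treat will be used, including all randomized parent-infant dyads in the analysis".

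Three other places bear on who might be found non-adherent:

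- Table 1, under Eligibility criteria, says of group 3: "The parents are also instructed to hum a lullaby with their infant". It asks for this from 10 minutes before the venipuncture until after it, and specifies style and sound level.
- The Discussion warns: "Parents might feel shy and inhibited about singing, especially in unfamiliar situations among unfamiliar people".
- The section Interventions notes that "standard of care in one of the hospitals does not include glucose but comprises only SSC and breastfeeding when applicable".

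**The concern.** Adherence in the allocated group can be judged only once the allocation is known and the regimen has been offered. Every exclusion under this rule is therefore made after randomization. The article also says that the nurse and parents cannot be blinded during the procedure, so the judgement is made by people who know the group.

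The groups ask different things of the parent. Group 1 needs glucose, tucking and the examination table. Group 3 needs skin-to-skin contact and sustained humming, with breastfeeding where applicable. The infants excluded may therefore differ between arms in number and in kind. The hypothesis and the sample size both concern group 3 against standard care, so any such selection falls on the main comparison. Scoring PIPP-R blind from muted video does not help, because the selection concerns which infants are scored at all.

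The rule also governs conduct. PIPP-R is taken over the first 30 seconds of a single procedure. If staff read exclusion from the study as a reason to stop recording, the outcome is lost and no later analysis plan can recover it.

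**Working it through.** **1. The two rules side by side.** Take a dyad that is randomized to group 3 and whose parent does not hum.

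| Rule | Consequence for this dyad |
|---|---|
| Recruitment and allocation | removed from the study |
| Data analyses, management and monitoring | included in the analysis, in group 3 |

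The article names no per-protocol or modified intention-to-treat set, and it does not say that data from excluded infants are kept. Both rules cannot be met. This step needs no arithmetic, and the finding rests on it alone.

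**2. The plan's own figure.** The section Sample size gives a difference of 2 points, an SD of about 2, power 0.8 and significance level 0.05, and states: "A power calculation sets the number of infants to include in the study to 63 in each group". It then enrols 75 per group. The usual two-sided formula is n = 2 × ((1.960 + 0.842) × SD / difference)².

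- SD 2: 2 × (2.802 × 2/2)² = 15.7, that is 16 per group.
- SD 4: 2 × (2.802 × 4/2)² = 62.8, that is 63 per group.

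The stated inputs do not give 63. It corresponds to a standardized effect of 0.5. That is a separate matter, but it means the cost of the fix should be shown at both SDs.

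**3. Bias if infants are excluded.** Let f be the share of an arm excluded and d the mean score difference between excluded and kept infants. The kept mean differs from the mean of the whole arm by f × d. The article gives neither quantity, so both are assumed.

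| f (of 75) | d = 1 | d = 2 | Share of the 2-point target |
|---|---|---|---|
| 5% (about 4) | 0.05 | 0.10 | 2.5% to 5% |
| 10% (about 7) | 0.10 | 0.20 | 5% to 10% |
| 20% (15) | 0.20 | 0.40 | 10% to 20% |

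If both arms lose 10%, the net bias is 0 when the shifts are equal and in the same direction. When they are opposite it is 0.2 (d = 1) or 0.4 (d = 2).

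**4. Dilution if infants are kept.** As an assumed worst case, a share f of one arm loses the whole 2-point effect. The contrast becomes 2 × (1 − f). The SD of that arm becomes √(SD² + 4f(1 − f)). Power is for a two-sided Welch t-test at 0.05.

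| f | Contrast | SD 2, 75 per arm | SD 4, 75 per arm | SD 4, 63 per arm |
|---|---|---|---|---|
| 0 | 2.0 | >0.999 | 0.860 | 0.795 |
| 5% | 1.9 | >0.999 | 0.822 | 0.751 |
| 10% | 1.8 | >0.999 | 0.777 | 0.703 |
| 20% | 1.6 | 0.997 | 0.674 | 0.597 |

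At SD 2 with 63 per arm, power is still about 0.99 at f = 20%. For comparison, excluding 10% of one arm at SD 4 (68 against 75, contrast still 2) gives 0.843.

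**The case against.** The strongest reply accepts the conflict and disputes its weight.

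- **Non-adherence may be rare.** The task is one short procedure. Parents in group 3 see a demonstration video and receive verbal guidance. The Discussion reports that 60% of parents already sing spontaneously to their newborn in hospital. This stands: nothing in the article supports a rate as high as 20%, so the top of the bias range may be remote.
- **Its scope is narrow.** Breastfeeding in group 3 applies only where applicable, and group 2 is split to accommodate the mother's choice, so not breastfeeding need not count as non-adherence. This also stands. Humming is the one clear risk the article names. A group 1 mother breastfeeding at the hospital without glucose is conceivable, but it is an inference.
- **The power cost was worked with all 75 per arm**, although the 12 beyond 63 are there for dropouts and incomplete data. That is fair, and the column for 63 per arm answers it.
- **An analysis plan or the full protocol could settle it.** This does not stand. The article does not leave the point open: it states two opposing rules. Reading the exclusion as per-protocol only has no support in its wording, which removes the infant from the study.

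**Conclusion.** Wrong as written. The exclusion for non-adherence and the promise of intention-to-treat in all randomized dyads contradict each other, and the analysis set for a non-adherent dyad is undetermined. That conclusion is certain and depends on no assumption.

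The consequence is less certain. Following the exclusion would introduce selection of unknown direction into the group 3 versus group 1 contrast. Under the assumed inputs, exclusion from one arm shifts the contrast by 0.05 to 0.4 points against a target of 2, so a bias large enough to overturn a conclusion has not been shown. The point should be corrected because it touches the main comparison and the correction is simple.

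**What to change.** Delete the exclusion sentence under Recruitment and allocation. In its place, state that a dyad whose parent does not carry out the allocated regimen stays in the study, is filmed and scored as planned, has the departure noted, and is analysed in its allocated group. Randomized dyads without outcome data (withdrawal, equipment failure) should be reported by group with the reason, since an analysis of those with data is not strictly one of all randomized dyads. If an adherent-only analysis is wanted, label it a per-protocol sensitivity analysis and define non-adherence in advance for each group.

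The cost is a sentence or two of text and no added infants. The recordings already planned for every dyad must be completed and scored for non-adherent dyads too. The statistical price is dilution. At the stated SD of 2, power stays at about 0.99 or higher even with 20% non-adherence. At SD 4 it can be material: with 75 per arm, power falls from 0.86 to 0.78 at 10% and to 0.67 at 20%, and it is lower still with 63.
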